## 7. Outcomes

Primary outcome: mortality by Day-14. Day-0 is the day of the first dose of favipiravir.

Secondary outcomes:

- Mortality by Day-14 according to the second group definition (AC1, AC2, YC).

All the following outcomes will be analyzed overall and separately by the two group definitions (A1, A2, C or AC1, AC2, YC):

- Evolution of EBOV plasma RNA and infectious loads (sampling time depending of the group);
- Occurrence of grade 3 or 4 clinical or biological adverse events (Common Terminology Criteria for Adverse Events, CTAE, v3.0);
- Evolution of viral micro-diversity of EBOV (including potential resistance mutations);
- Plasma trough concentrations of favipiravir (sampling time depending of the group);
- Criteria for cure at Day-30 (end of follow-up visit);
- Factors associated with mortality and toxicity (including time from first symptoms to treatment initiation; evolution of EBOV RNA and infectious loads after treatment initiation and trough concentrations of favipiravir).

## 8. Trial conduct

### 8.1 Sponsor and coordination

The trial sponsor is the INSERM. The international coordinating, monitoring and data management centre will be the Mereva clinical trial unit (CTU), an international team with members affiliated to the Inserm 897 Unit, University of Bordeaux and to the Pacci/ANRS research site in Abidjan. Trial coordinating, monitoring and data management activities will be coordinated by an International Clinical Project Manager (CPM). In Guinea, where the trial will be conducted, a trial country coordination center (CCC) will be put in place, lead by a country CPM who will work in close collaboration with the international CPM and with the participating clinical centres.

The trial will be conducted and monitored according to a Standard Operating Procedures (SOPs) manual.

### 8.2 Trial drug

Favipiravir tablets are light yellow, round-shaped, coated divisible tablets containing contain 200 mg of favipiravir drug substance. They can be crushed and mixed with liquid, provided this is done just before the administration.

Favipiravir is rapidly and completely absorbed after oral administration. The major metabolite is inactive and excreted predominately in the urine. Food does not appear to alter the absorption of the current tablet formulation.

Drug-drug interactions were identified with pyrazinamide, repaglinide, theophylline, and sulindac. None of these drugs are part of the standard package of care currently used in EVD care centres.

The investigator's brochure is attached to the protocol.

### 8.3 Trial development and scheduled assessment

Once the trial is opened, all patients who attend the trial centers will be assessed for inclusion and non-inclusion criteria. Those who fulfill inclusion criteria will be informed and proposed to participate. Those who accept will be asked for informed consent.

- **Trial treatment:**

- Adults (groups A1 and A2): Day-0, H0: 2400 mg (12 tablets); H8: 2400 mg (12 tablets); H16: 1200 mg (6 tablets). Day-1 to Day-9: 1200 mg (6 tablets) bid.
- Children (group C): The loading dose (Day 0) and the dose from Day-1 to Day-9 will be adapted to the body weight (*see Table I*).

- **Other treatments:** From Day-0 to end of follow-up, all participants will receive the standard package of care, as defined by the care providers. This will be the object of a data collection, but will not be imposed by the protocol.
- **Blood collection** (see Tables 2 and 3):
  - Adults (groups A1 and A2): blood will be collected in 4 ml trial tubes during: (i) routine care venepuncture (Day-0, end of symptoms (EOS)+72h); (ii) additional trial venepuncture at: Day-2, Day-4, Day-13 and Day-30.
  - Children (group C): blood will be collected in 4 ml trial tubes during: (i) routine care venepuncture (Day-0, EOS+72h); (ii) additional trial venepuncture at Day-2, Day-4, Day-13 and Day-30.

**Table 2: assessment schedule in adults**

|                     | Clinical examination | Favipiravir (mg) | Blood collection | Additional venepuncture** | Additional laboratory manipulation*** |
|---------------------|----------------------|------------------|------------------|---------------------------|---------------------------------------|
| Day-0               | x                    | 6000 ‡           | 1 RCT + 1 TT *   | No                        | Yes                                   |
| Day-1               | x                    | 1200 x 2         | No               | No                        | No                                    |
| Day-2               | x                    | 1200 x 2         | 1 TT *           | Yes                       | Yes                                   |
| Day-3               | x                    | 1200 x 2         | No               | No                        | No                                    |
| Day-4               | x                    | 1200 x 2         | 1 TT *           | Yes                       | Yes                                   |
| Day-5 to Day-9      | x                    | 1200 x 2         | No               | No                        | No                                    |
| Day-10 to discharge | x                    | No               | No               | No                        | No                                    |
| EOS+72h             | x                    | No               | 1 RCT + 1 TT *   | No                        | Yes                                   |
| Day-13              | x                    | No               | 1 RCT            | No                        | No                                    |
| Day-30              | x                    | No               | 1 TT *           | Yes                       | Yes                                   |

EOS: end of symptoms; ‡ H0: 2400 mg; H8: 2400 mg; H16: 1200 mg;

\* RCT: routine care tube; TT: trial tube (4 ml EDTA tubes); \*\* Venepuncture not included in routine care;

\*\*\* Tube centrifugation and cryoconservation.

**Table 3: assessment schedule in children**

|                     | Clinical examination | Favipiravir | Blood collection | Additional venepuncture** | Additional laboratory manipulation*** |
|---------------------|----------------------|-------------|------------------|---------------------------|---------------------------------------|
| Day-0               | x                    | Yes ‡       | 1 RCT + 1 TT *   | No                        | Yes                                   |
| Day-1               | x                    | Yes ‡       | No               | No                        | No                                    |
| Day-2               | x                    | Yes ‡       | 1 TT *           | Yes                       | Yes                                   |
| Day-3               | x                    | Yes ‡       | No               | No                        | No                                    |
| Day-4               | x                    | Yes ‡       | 1 TT *           | Yes                       | Yes                                   |
| Day-5 to Day-9      | x                    | Yes ‡       | No               | No                        | No                                    |
| Day-10 to discharge | x                    | No          | No               | No                        | No                                    |
| EOS+72h, or Day-12  | x                    | No          | 1 RCT + 1 TT *   | No                        | Yes                                   |
| EOS+96h, or Day-13  | x                    | No          | 1 RCT *          | No                        | No                                    |
| Day-30              | x                    | No          | 1 TT *           | Yes                       | Yes                                   |

EOS: end of symptoms; ‡ Dosages adapted to the body weight (see Table 1);

\* RCT: routine care tube; TT: trial tube (4 ml EDTA tubes); \*\* Venepuncture not included in routine care;

\*\*\* Tube centrifugation and cryoconservation.

According to the European ethical recommendations, the trial-related blood loss will not exceed 3% of the total blood volume overall (2.4 ml blood per kg body weight) and will not exceed 1% at any single time.

- **Hospital stay:**

All patients will be hospitalized in the isolation ward of the EVD care center until Day-14, including patients who reach criteria for cure before Day 14. Patients who meet criteria for cure before Day 14 or at Day 14 will be discharged at Day 14. Other patients will be hospitalized until criteria for cure are met.

Criteria for cure are the following:

- 4 days without fever or significant symptoms AND;
- able to feed and walk independently AND;
- two consecutive negative qualitative PCR.

- **End-of-follow-up visit:**

Patients discharged before Day-30 will be asked to show up at the trial center at Day-30 to undergo the end-of-follow-up visit. The visit will consist of a clinical examination and a blood sample collection. In the event of a patient being symptomatic at this visit, examination-guided tests will be performed and appropriate treatments will be given. If patients fail to report at Day-30, they will be contacted by phone or visited at home.

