**Blood collection:**

- Adults (groups A1 and A2): blood will be collected in 4 ml trial tubes during: (i) routine care venepuncture (Day-0; end of symptoms (EOS)+72h); (ii) additional trial venepuncture at: Day-2, Day-4, Day-13 and Day-30.
- Children (group C): blood will be collected in 4 ml trial tubes during: (i) routine care venepuncture (Day-0, EOS+72h); (ii) additional trial venepuncture at Day-2 Day-4, Day-13 and Day-30.

**Biology:** *In trial settings laboratories:* At Day-0, Day-2 Day-4, Day-13 the following tests will be done: qualitative PCR (Altona qualitative RT-PCR commercial kit); and biochemical tests (creatininemia and others tests according to local choice), if biochemical tests are doable in the laboratory. At Day-30 the following tests will be done: biochemical tests (creatininemia and others tests according to local choice) only if tests at Day-13 were abnormal *Outside trial settings laboratories:* all trial tube will be shipped frozen in triple-layer packaging to the Lyon-Mérieux BSL4 laboratory, where the following tests will be done: quantitative PCR (standard real-time RT-PCR procedures, synthetic RNA quantified external calibrators), infectious viral load (standard procedure with serial sera dilutions and infection of Vero cells), viral subpopulations (next-generation sequencing methods), drug concentrations measurement (HPLC), uricemia, and other biochemical tests (transaminases, creatininemia, natremia and kaliemia), if biochemical tests have not been done in the trial setting laboratory.

**Sample size:** recruitment in the trial will be kept opened in all groups\* until group A1 reaches 60 participants (\*unless early termination is recommended by the DSMB).

**Statistical analysis for primary outcome:** mortality by Day-14 with exact 95%CI will be reported overall and in each group separately.

In group A1, if the number of deaths is <24 (40%) out of 60 participants, the upper bound of the 95%CI will be <55%.

In group A2, if the number of deaths is <54 (45%) out of 120 participants, the upper bound of the 95%CI will be <55%.

In group C, if the number of deaths is <17 (38%) out of 45 participants, the upper bound of the 95%CI will be <55%.

In each group (A1, A2, C), we will conclude that favipiravir decreases mortality if the upper bound of the 95% CI does not include the observed pre-trial mortality (55%) in untreated patients with same duration of symptoms prior to trial initiation.

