### 2.8.2 Children

So far no children have been exposed to favipiravir. Juvenile toxicity animal's studies have shown higher level of toxicity with lower exposure as compared to adult animals. However, it is difficult to extrapolate these findings to children.

Below 12 months of age and below 10 kg, drug disposition is difficult to predict for favipiravir. Therefore, we will not include infants below 12 months or below 10 kg in order to avoid inaccurate prediction of drug levels and limit the potential risk of drug overdose.

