### 6.2 Groups

In this protocol, we will refer to the following groups according to age and duration of symptoms\*:  
Group A1: adults with time between first symptoms and first dose of favipiravir  $\leq 72$ h; Group A2: adults with time between first symptoms and first dose of favipiravir  $> 72$ h and Group C: all children  $\geq 1$  year and weighting  $\geq 10$ kg. Time of first symptom refers to the time of the beginning of any symptom considered to be related to EVD.

\* Symptoms to be considered will be: acute onset of fever, severe headache, myalgia, extreme fatigue, vomiting, diarrhoea, abdominal pain, or unexplained hemorrhage.

The division in groups is a matter of analysis, and will not be perceptible by the patients during the trial process. Patients in the three groups will receive the same treatment and will be followed under the same procedures. Daily dosages will be adapted to the body weight in group C.

A second definition of group was also used: group AC1: adults and children  $> 6$  years with baseline Ct  $\geq 20$ ; group AC2: adults and children  $> 6$  years with baseline Ct values  $< 20$ ; group YC: young children  $\leq 6$  years and  $\geq 1$  year.

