### **9.2 Other outcomes**

Mortality by Day-14 with exact 95%CI will be reported according to the second group definition (AC1, AC2, YC). In each group, we will conclude that favipiravir decreases mortality if the upper bound of the 95% CI does not include the observed pre-trial mortality (30%, 85% and 70%, respectively) in untreated patients with same characteristics of symptoms prior to trial initiation (*see section 6.3*).

All the following outcomes will be reported overall and separately by the two group definitions (A1, A2, C or AC1, AC2, YC).

The evolution of EBOV plasma RNA and infectious loads between Day-0 and the end of follow up will be described in each patient. The numbers, proportions and exact 95% CI will be described for grade 3-4 adverse events; resistance mutations; and patients reaching criteria for cure at Day-30. The distribution (median, IQR, min-max) of initial and maximal viral load, time to maximal viral load and to undetectability, and rate of increase/decrease will be reported. The distribution of trough concentrations of favipiravir at each point and the inter- and intra-patient variability of concentrations will be described.

Factors associated with mortality by Day-14, cure at Day-30 and grade 3-4 clinical or biological adverse events (including time between first symptoms and treatment initiation, evolution of EBOV viral load, trough concentrations of favipiravir) will be studied.

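### The cure definition asks every patient to walk and feed independently, with no age or pre-illness qualifier, so some recovered toddlers would be scored as not cured at Day-30

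*Protocol*

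**What the plan says.** Protocol section 8.3 (Hospital stay) and the Synopsis (Follow-up) give one list of cure criteria for all patients. It has three parts joined by AND: a period free of fever and significant symptoms, the functional item "able to feed and walk independently AND", and two negative PCR results in a row. Neither place adds an age qualifier or refers to what the patient could do before the illness.

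Enrolment starts at 1 year and 10 kg (section 6.1). Section 2.8.2 puts the floor as "we will not include infants below 12 months or below 10 kg". Section 6.2 states "Patients in the three groups will receive the same treatment and will be followed under the same procedures" and adapts only the dosages in group C. Table 3 changes some sampling times for children but gives no paediatric version of cure.

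The list has two uses. It is a secondary outcome in section 7, "Criteria for cure at Day-30 (end of follow-up visit", and section 9.2 reports the number, proportion and exact 95% CI of "patients reaching criteria for cure at Day-30", under the instruction "All the following outcomes will be reported overall and separately by the two group definitions (A1, A2, C or AC1, AC2, YC". It also governs discharge after Day-14: "Other patients will be hospitalized until criteria for cure are met".

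**The concern.** A child just over 12 months may not yet walk, and may not yet eat without help. For such a child the functional item is false before Ebola and can still be false after full recovery. Because the items are joined by AND, that child is then scored as not cured because of developmental stage, not disease.

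The error runs in one direction only. It falls in group C and in group YC, which holds ages 1 to 6 and so concentrates the youngest patients. Groups A1, A2, AC1 and AC2 contain no toddlers. Cure proportions in C and YC would be somewhat too low, and their comparison with the older groups would mix recovery with age. An analysis plan cannot repair this afterwards unless pre-illness function has been recorded.

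**Working it through.** There is no stated sample size, power or error rate to reproduce. The check has a textual part and an illustration of scale.

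**Text.**
1. Cure needs all three items (Synopsis; section 8.3).
2. The youngest eligible patient is 12 months old and weighs 10 kg (sections 2.8.2 and 6.1).
3. Procedures are the same in all groups and only dosages are adapted (section 6.2).
4. No other section defines the functional item or limits it by age.
5. So a symptom-free, twice PCR-negative child who does not walk or self-feed at Day-30, and did not before the illness, fails item two and is counted as not cured.

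**Scale in group C.** The inputs come from the Synopsis: "In group C, if the number of deaths is <17 (38%) out of 45 participants". Take 45 children and 17 deaths, leaving 45 − 17 = 28 survivors. Assume all 28 survive to Day-30 and recover. Let k be the number of recovered children who fail only the functional item for developmental reasons; k is an assumption, since the protocol gives no such count. The scored cure proportion is (28 − k)/45, so each child costs 1/45 = 2.2 points. Exact (Clopper-Pearson) 95% intervals:

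| k | Scored as cured | Proportion | 95% CI |
|---|---|---|---|
| 0 | 28/45 | 62.2% | 46.5 to 76.2 |
| 1 | 27/45 | 60.0% | 44.3 to 74.3 |
| 2 | 26/45 | 57.8% | 42.2 to 72.3 |
| 3 | 25/45 | 55.6% | 40.0 to 70.4 |
| 5 | 23/45 | 51.1% | 35.8 to 66.3 |

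**Scale in YC.** The protocol gives no size for YC. At assumed sizes of 10, 15 and 20, one child costs 1/10 = 10.0, 1/15 = 6.7 and 1/20 = 5.0 points.

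**How many children might be affected, for walking.**
- Sections 2.1 and 2.4 put under-5s at 3.6 to 6.3% of admissions.
- The Synopsis examples total 60 + 120 + 45 = 225 patients.
- 225 × 0.036 = 8.1 and 225 × 0.063 = 14.2 under-5s, some of them infants who are not eligible.
- If one-fifth are aged 12 to 23 months (assumption): 1.6 to 2.8 children.
- At the 70% pre-trial mortality for YC (section 6.3), 30% survive: 0.5 to 0.85 children.
- At the group C example instead, 28/45 = 62.2% survive: 1.0 to 1.8 children.

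These counts come before the 10 kg floor is applied, and only some of these children would not yet walk. About one affected survivor or fewer is a fair working figure for walking. For self-feeding the documents give nothing from which to count.

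**The case against.** The strongest reply is that the wording is loose, not wrong. Feeding independently is undefined and could mean eating without a tube or medical help, which a healthy toddler would satisfy. The literal reading also leads to an implausible result on the ward, which suggests that recovered function was meant. The standard operating procedures and the case report form, which are not shown, may say so. Part of this stands: intent is probably sensible. But the walking half is less open to a loose reading, and an undefined item lets two investigators score the same child differently.

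A reader might infer three stronger things that the documents do not support.

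- **That such a child can never be scored as cured.** A child close to the milestone may reach it by Day-30. The claim holds only for one who still has not.
- **That young age is bound to emerge as a factor against cure because of this item.** Section 9.2 does not list age among its named factors, although the list is open. The assumed 70% mortality in YC already ties young age to non-cure through death. The scoring error would at most add a little.
- **That cure in YC would fall by a large fraction.** That needs an assumed group size and an assumed one or two affected survivors. The protocol gives neither, and its own admission shares point to a smaller number.

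It is also fair to say that cure at Day-30 is descriptive, with no threshold attached, and that section 2.4 concedes weak power for efficacy in children. That limits the severity but does not make the definition right.

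**Conclusion.** The point holds, at minor severity. As written, the functional item misclassifies a recovered child who did not walk or self-feed before illness and still does not at Day-30, and the protocol deliberately enrols the age at which this can happen. The effect is a downward bias in the Day-30 cure proportion of 1/n per child: 2.2 points at 45 children in group C, and 10.0 to 5.0 points if YC has 10 to 20 children (assumed sizes).

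The likely count is small. Shifts from one to three such children in group C lie well inside the exact interval of 46.5 to 76.2%. The conclusion rests on the literal text and on the assumption that some enrolled children of about 12 to 23 months do not yet walk or self-feed. The primary outcome and every decision rule are untouched.

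Separately, the discharge sentence in section 8.3 relies on the same list, so read literally it does not fit a recovered child of this kind. The sponsor must reconcile that text with the inclusion of children from 1 year. Nothing here says what the discharge rule should be.

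**What to change.** For scoring the Day-30 cure outcome only (sections 7, 8.3 and 9.2), define the functional item as return to the patient's pre-illness ability to walk and to feed, so that it counts as met where the ability was absent before the illness. Record that ability at Day-0, as yes or no, from the patient or the guardian. The same wording would cover an older patient who could not walk before Ebola, should one be enrolled. Report how many patients change status between the present wording and the new one, so that readers can see the size of the effect.

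The cost is one sentence in the outcome definition and one case report form item, with no added visit, sample or venepuncture. The downsides are small: the item relies on recall, and the scoring definition must be labelled as distinct from the criteria used for discharge. The discharge passage is for the sponsor to reconcile with the age range as a separate matter.

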## 8.4 Biology

*In trial settings laboratories:*

- At Day-0, Day-2 Day-4, Day-13 the following tests will be done: qualitative PCR (Altona qualitative RT-PCR commercial kit); and biochemical tests (creatininemia and others tests according to local choice), if biochemical tests are doable in the laboratory.

- At Day-30 the following tests will be done: biochemical tests (creatininemia and others tests according to local choice) only if tests at Day-13 were abnormal.

- EDTA tubes will be decanted, and the serum will be divided into two aliquots of up to 1 ml. Aliquots will be frozen at -20 °C.

*Outside trial settings laboratories:* all trial samples will be centrifuged and frozen on the day of collection. They will be used for virological tests that are currently not available in Guinea and that need to be done in a Biosafety level 4 laboratory. Therefore, they will be shipped frozen to the Lyon-Mérieux BSL4 laboratory, using international standard procedures, including triple-layer packaging (collection tube, plastic waterproof boxes, special cartoon box with the international label for transport of Infectious Substances: UN6.2 class A, UN2814), and disinfection procedures for the outside of the tube and inside/outside of the box and of the cartoon. A Material Transfer Agreement will be obtained by the sponsor.

In the BSL4 laboratory, Quantitative RT-PCR will be performed using a standard real-time RT-PCR procedure and a set of synthetic RNA quantified external calibrators. The infectious load will be evaluated by determining the number of infectious viral particles using a standard procedure relying on serial dilutions of sera and infection of Vero cells. Evolution studies will rely on the analysis of the kinetics of viral subpopulations as determined using next-generation sequencing methods. In brief, a series of overlapping PCR products spanning the complete genome will be generated using a high fidelity amplification protocol and sequenced using the Ion Torrent NGS platform. After quality check and trimming primer sequences, complete genome sequences will be rebuilt and used for sub-population analysis.

The following tests will also be made in the Lyon-Mérieux BSL4 laboratory:

- Concentrations measurement will be made by HPLC using methods provided by the manufacturer of the drug.
- Uricemia
- Other biochemical tests: liver enzymes, creatininemia, natremia and kaliemia (expect if the tests have been made in the setting laboratory).

These tests will be completed within the six months following collection. Any remaining material will be stored in Lyon-Mérieux BSL4 laboratory for 10 years. Any future use will be approved by the committees that gave approval to the initial study. These samples will only be used in the framework of non-commercial research.

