## 2.8 Toxicity issues

### 2.8.1 Adults

So far, about 2000 subjects received at least one dose of favipiravir during the clinical development of the drug for the treatment of influenza. Among them, several hundred received a loading dose of 3600 mg (1800 mg bid or 2400 mg, 600 mg, 600 mg administered on an 8h schedule). Side effects were rare, and included diarrhea (2.8%), asymptomatic hyperuricemia (1.5%), asymptomatic increase in liver enzyme (AST, ALT, gamma-GT) (1.3%), asymptomatic decrease in neutrophil counts and white blood cells, headache, asymptomatic increase in triglycerides (1%), vomiting, dizziness and proteinuria (0.9% each). Details from the investigator's brochure are available in Appendix 6.

Based on non clinical data, three additional issues have been raised:

- QT prolongation: positive findings were shown on the hERG channels. Consequently a dedicated QT/QTc study was performed in healthy adult volunteers with a single dose of 2400 mg. Although this study was negative, the potential risk of QT prolongation cannot be strictly ruled out in the context of EVD (higher doses, diarrhea with dyskaliemia).

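### Fallback sodium and potassium are measured on EDTA plasma (wrongly called serum), so at least one of the two cannot be graded as an adverse event

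*Protocol*

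**What the plan says.** The footnotes to Tables 2 and 3 define the only tube used for trial samples: "TT: trial tube (4 ml EDTA tubes". Section 8.4 then states that "EDTA tubes will be decanted, and the serum will be divided into two aliquots of up to 1 ml", and that the aliquots are frozen. According to the Biology paragraph of the synopsis, "all trial tube will be shipped frozen in triple-layer packaging to the Lyon-Mérieux BSL4 laboratory".

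Among the tests at that laboratory, section 8.4 lists "Other biochemical tests: liver enzymes, creatininemia, natremia and kaliemia (expect if the tests have been made in the setting laboratory". The synopsis sets the same condition: "natremia and kaliemia), if biochemical tests have not been done in the trial setting laboratory". On site, creatinine is the only biochemical test named. Other tests are left to local choice, and all of them depend on what the laboratory can do.

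Section 7 lists as a secondary outcome "Occurrence of grade 3 or 4 clinical or biological adverse events". Section 9.2 reports these events with exact 95% confidence intervals and studies associated factors. Section 2.8.1 gives a reason to care about potassium: "the potential risk of QT prolongation cannot be strictly ruled out in the context of EVD (higher doses, diarrhea with dyskaliemia". Section 8.5.3 adds that electrocardiograms cannot be done.

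**The concern.** An EDTA tube keeps blood from clotting, so what is decanted is plasma; section 7 itself speaks of plasma RNA and plasma concentrations. The wrong word changes no result. The tube does matter. A standard EDTA salt carries potassium or sodium, and the protocol assigns both ions to be measured in that fluid whenever the site has no value. For the ion in the additive, the result reflects the tube as well as the patient.

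At stake is the count of grade 3-4 biological events. A contaminated value could be graded as a false high event, or a true low value could be hidden. If such values are discarded instead, the denominator shrinks with no rule for reporting it.

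**Working it through.** The plan gives no figure to reproduce. The check has two parts: tracing the sample through the text, and a mass balance for the ion that the tube adds.

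**Trace.**
1. Trial tube: 4 ml EDTA in adults and children, salt not stated (Tables 2 and 3).
2. Fluid: decanted from those tubes, aliquoted and frozen (section 8.4).
3. Shipped material: trial tubes only (synopsis, Biology). No shipment of a routine care tube is described.
4. Tests: sodium and potassium, if not done on site (section 8.4; synopsis).
5. Outcome: grade 3-4 biological adverse events, with no electrolyte named and none excluded (sections 7 and 9.2).

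No step provides another tube for the fallback electrolytes.

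**Mass balance.** Assumptions, none of them in the protocol: 1.2 to 2.0 mg EDTA salt per ml blood, tube filled to volume, dihydrate salts, haematocrit (Hct) 0.30 to 0.45, added ion confined to plasma.

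Added ion in plasma (mmol/l) = (mg per ml ÷ molar mass × 1000 × cations per molecule) ÷ (1 − Hct)

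| Salt (molar mass, cations) | 1.2 mg/ml, Hct 0.30 | 2.0 mg/ml, Hct 0.45 |
|---|---|---|
| K2EDTA (404.5, 2) | 5.9 ÷ 0.70 = 8.5 potassium | 9.9 ÷ 0.55 = 18.0 potassium |
| K3EDTA (442.5, 3) | 8.1 ÷ 0.70 = 11.6 potassium | 13.6 ÷ 0.55 = 24.7 potassium |
| Na2EDTA (372.2, 2) | 6.4 ÷ 0.70 = 9.2 sodium | 10.7 ÷ 0.55 = 19.5 sodium |

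**Reading the result.** Take a normal potassium of about 4 mmol/l (assumed). With a potassium salt, even a true value of zero would read at least 8.5, about twice normal, so low potassium cannot show. A normal value would read between 4 + 8.5 = 12.5 and 4 + 24.7 = 28.7. No fixed correction can be subtracted, because the shift varies with tube content and haematocrit: by 18.0 − 8.5 = 9.5 mmol/l for K2EDTA and 24.7 − 11.6 = 13.1 for K3EDTA. For a sodium salt the spread is 19.5 − 9.2 = 10.3 mmol/l. A potassium salt adds no sodium, and a sodium salt adds no potassium.

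**Visits.** Section 8.4 plans on-site biochemistry at Day-0, Day-2, Day-4 and Day-13. At Day-2 and Day-4, Tables 2 and 3 list one trial tube and nothing else, so an on-site electrolyte on those days would also come from EDTA unless another tube is drawn. At Day-13 the tables list only a routine care tube without extra venepuncture, while section 8.3 lists Day-13 among the additional trial venepunctures. Whether a fallback sample exists on that day is therefore unclear. The type of the routine care tube is not stated.

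**The case against.** The best defence is that tube additives and specimen rejection are laboratory matters. Section 8.1 refers to a manual of standard operating procedures that is not shown, and a potassium shifted this far would probably be recognised and discarded. That is plausible, but section 8.4 itself pairs the tube with the tests, and a procedure that dropped potassium would depart from it. Discarding would also leave the denominator for electrolyte events undefined.

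It is also fair that no sentence says the BSL4 electrolytes will be graded. Sections 7 and 9.2 name no electrolyte. The link to the outcome is that these are biological test results and the outcome counts biological events without excluding any.

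Three stronger readings might be inferred, and the protocol does not support them:
- *Both electrolytes are lost.* The additive spoils only the ion that it contains, and the salt is not stated. With a sodium salt, the dyskaliemia argument falls away.
- *The tubes are mislabelled.* The tubes are correctly called EDTA throughout; only the separated fluid is misnamed.
- *Monitoring for QT risk fails because of this.* Section 8.4 allows six months for the BSL4 tests, so these values could hardly stand in for an electrocardiogram in time to matter.

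**Conclusion.** The point holds in a limited form. As written, the plan yields an invalid fallback value for at least one of sodium and potassium, and for potassium if the tubes hold a potassium salt. The size, about 8.5 to 25 mmol/l potassium or about 9 to 20 mmol/l sodium, rests on the assumed salt, concentration and haematocrit; the protocol supplies none of them.

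The reach is electrolyte events within one secondary safety outcome, in patients without a valid on-site value. How many that is cannot be derived. It may be none or all of a site's patients, and it is not confined to sites without biochemistry, since a site that measures creatinine may still not measure electrolytes.

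**What to change.** 1. In section 8.4, replace serum with plasma and state the additive of the trial tube.
2. Remove the ion contained in that additive from the tests run on EDTA aliquots, or exclude it from grade 3-4 grading. Apply this to on-site and BSL4 measurements alike, because Day-2 and Day-4 have only an EDTA tube.
3. Count that electrolyte only from a tube whose additive does not contain it. Restricting the count to routine care tubes is not a safe shortcut: their type is not stated, and none is listed at Day-2 or Day-4.
4. Report the number of patients with a valid value as the denominator for that electrolyte.
5. Reconcile the Day-13 tube in section 8.3 with Tables 2 and 3.

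These are changes of wording and need no extra tube. The cost is fewer patients and time points with a gradable value for that electrolyte, mainly at Day-2 and Day-4, which are the scheduled samples after Day-0 within the dosing period. Adding a suitable tube on those days would recover them, but it must fit the blood limit under Table 3. For a 10 kg child the overall limit is 2.4 × 10 = 24 ml, and the five trial tubes in that table already take 5 × 4 = 20 ml if filled.
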